### Data collection and participant timeline

The participant timeline is displayed in Fig. 2. Subject retention is being addressed through the following methods: extensive contact information will be recorded for each participant and the research coordinator will call before each study visit to encourage attendance. Additionally, participants are contacted and encouraged by the research coordinator to report any serious adverse events as they occur, while any other adverse event reporting occurs at the next available study visit or scheduled phone check in. Participants are being reimbursed for their time and reasonable travel expenses necessary for their participation. Non-adherence with therapy is being minimized by emphasizing the importance of compliance with study drug treatment and performing pill counts at study visits. If a participant wishes to drop-out from the treatment phase of the study or has a serious adverse event, we will continue to follow-up with the subject for study assessments to assist with safety monitoring and to avoid the problems introduced by missing data. Any missing data that will be reported as a protocol deviation to the single IRB and any other relevant monitoring authorities.

**Fig. 2 Fig2:**
[figure not shown]
Participant timeline and schedule of events. SF-36 = Short Form 36 questionnaire; MRI = magnetic resonance imaging; NT-proBNP = N-terminal pro B-type natriuretic peptide. ^*^: The right heart catheterization that is used for inclusion into the trial was done prior to enrollment as part of clinical care

### Specimen collection and storage

In addition to the laboratory tests to be run locally at each visit, research blood is being collected and processed by the research coordinator at each site. Those research collections are processed the same day as the visit and are stored initially at -80 degrees Celsius in freezers at the local site. The processed samples are then transported at a later date to the central JHU Scleroderma Biorepository for long term storage.

### Statistical methods

#### Sample size

We have based our effect size estimate of 45 m upon our preliminary data (not shown) demonstrating a difference in mean 6MWD between SSc patients with normal mPAP and SSc-MEP of ∼ 50 m with a standard deviation of 75 m. As such, we will have > 80% power to detect this difference at significance level of 0.05 with 27 subjects. To account for a 10% drop-out rate, we are enrolling 30 subjects. Even if our actual drop-out rate nearly doubles our expected rate (17% vs. 10%), we maintain adequate power to detect a difference of 45 m with 80% power (Fig. 3). While this estimate of change in 6MWD exceeds the MID for the 6MWD in PAH, the MID for this test in SSc-MEP is unknown. Further, if differences in 6MWD observed in the study do not reach the predefined detectable alternative, clinical relevance of the effect on 6MWD may be reflected by comparing the proportion of patients who exceeded the MID for 6MWD between arms. Based upon a sample size of 27 subjects completing the trial, we also have adequate power (80% or greater) to detect differences in the proposed secondary outcome measures. For instance, we have 80% power to detect a mean difference in PAC of 0.6 mL/mmHg (SD 1.1) between treatment arms; this difference was the average difference between these SSc-MEP and SSc-normal pressures found in our preliminary studies (data not shown). Further, we will have sufficient power to detect differences of 0.23 cm (SD 0.5) in TAPSE between groups which is close to the estimated MID for TAPSE in SSc-PAH (0.22 cm) from prior work from our group [28]. For global RV strain measured by STE, we have more than 85% power to detect a difference of 4.8% (SD 8%); this is the difference detected in our ATPAHSS Study of ambrisentan and tadalafil in treatment naïve SSc-PAH patients after therapy [28, 32]. Similarly, we have adequate power to detect a difference of 5% (SD 9%) in RVEF between arms; this difference is the MID for RVEF in PAH [35]. For HRQoL outcomes, we also have adequate power to detect clinically relevant changes in SF-36 of 5 units (SD 7 units) and emPHasis-10 of 6 units (SD 10) [36].

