While epidemiologic data show increased morbidity and mortality for persons with mildly elevated pulmonary artery pressures and guidelines now support lower thresholds for establishing the diagnosis of PH, there are no approved therapies for treatment of patients with this form of PH, which may substantially impact survival and progression to more severe PH. Only one prior trial has attempted to address this patient population. The EDITA study was a randomized controlled trial (RCT) of an endothelin receptor antagonist (ERA), ambrisentan versus placebo in 38 SSc subjects who either had SSc-MEP or an exercise-induced increase in mPAP [12]. Although the primary endpoint, change in mPAP after 6 months of treatment, was not different between the groups, the ambrisentan-treated participants had an improvement in resting pulmonary vascular resistance (PVR) and cardiac index (CI) change during exercise. Change in 6MWD also favored the ambrisentan group, with a 39-meter (m) improved compared to placebo [12]. This trial demonstrated the potential for a PAH medication to improve outcomes in SSc patients with mildly elevated mPAP but was limited by the mixed nature of the cohort and the selection of their primary endpoint, since mPAP is unlikely to change significantly due to the narrow range of pressures in SSc-MEP.

The lack of data examining the utility of vasodilator therapy in the management of SSc-MEP motivated the “**S**ildenafil Versus Placebo for **E**arly **P**ulmonary **V**ascular **D**isease **I**n **S**cleroderma” (SEPVADIS) Study. This study is a RCT of sildenafil versus placebo in SSc-MEP patients to investigate the following aims: (1) To determine whether sildenafil affects the 6MWD in SSc-MEP patients at 16 weeks and 1 year; (2) To determine if sildenafil affects RV function in SSc-MEP patients at 16 weeks; (3) To determine whether sildenafil affects health-related quality of life (HRQoL) in SSc-MEP patients at 16 weeks and 1 year.

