#### Data analysis plan

The intent-to-treat analysis will include all randomized subjects. Hypothesis testing will use two-sided α = 0.05 without correction for multiplicity. We will characterize subjects regarding baseline and follow-up 6MWD and other endpoints. We will summarize demographics and other predictors of clinical status. Continuous variables will be summarized by the mean, median, standard deviation, and range, as appropriate. The distribution of the outcome measures of interest will be assessed for normality. If the distribution is normal, we will use independent t-tests to compare by treatment assignment. If the distribution is not normal, we will transform the data to meet the assumption of normality. If transformation does not achieve normality, comparisons between groups will be made using the Wilcoxon rank-sum test. We will use contingency tables for discrete and dichotomous variables.

The primary analysis will compare the absolute change in 6MWD from baseline with adjustment for baseline 6MWD, age, and sex in linear regression models. We chose sex as a potential confounder of the relationship between 6WMD and treatment based upon prior work demonstrating there may be worse survival for men with SSc-PAH compared to women [37], but men may have improved 6MWD and HRQoL compared to women in response to PDE-5 inhibitors [38]. Given the small sample size of our study, we will be sensitive to overfitting our model with covariates but will use the univariate analyses to inform the inclusion of additional covariates in the final model. We will examine the clinical relevance of the change in 6MWD by comparing the proportion of patients who achieve the MID for the 6MWD for both PAH (MID = 33 m) and for SSc-PAH (MID = 24 m) by treatment assignment. Using separate multivariable logistic regression models adjusting for baseline walk distance, age, and sex, we will assess if the odds of achieving a clinically relevant improvement in 6MWD based upon the MID for PAH and for SSc-PAH differs by treatment assignment. We can then perform responder analyses to determine characteristics of SSc-MEP patients likely to achieve either MID for the primary outcome of 6MWD.

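### The 6MWD sizing takes 45 m and SD 75 m from a cross-sectional gap between disease groups, and power above 80% does not hold for the planned sildenafil-versus-placebo comparison

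*Protocol article*

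**What the plan says.** The Background defines the comparison: "This study is a RCT of sildenafil versus placebo in SSc-MEP patients". The Data analysis plan fixes the primary test: "The primary analysis will compare the absolute change in 6MWD from baseline with adjustment for baseline 6MWD, age, and sex". Interventions gives 1:1 allocation, and hypothesis tests are two-sided at 0.05.

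The Sample size section draws its effect from elsewhere: "We have based our effect size estimate of 45 m upon our preliminary data (not shown"), the data "demonstrating a difference in mean 6MWD between SSc patients with normal mPAP and SSc-MEP of ∼ 50 m with a standard deviation of 75 m". From this it claims more than 80% power with 27 subjects in total, and 80% power at 45 m even if drop-out reaches 17%. For pulmonary arterial compliance (PAC) it claims 80% power for 0.6 mL/mmHg (SD 1.1) between arms, and gives the origin of that figure: "this difference was the average difference between these SSc-MEP and SSc-normal pressures found in our preliminary studies".

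The article contains one placebo-controlled 6MWD figure, from the ambrisentan trial described in the Background: "Change in 6MWD also favored the ambrisentan group, with a 39-meter (m) improved compared to placebo". It is not cited as a basis for sizing. Outcomes gives MIDs of 33 m (PAH) and 24 m (SSc-PAH).

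**The concern.** A sample-size calculation needs the effect and the SD of the quantity that will be tested. Here that is the difference between sildenafil and placebo, within SSc-MEP, in 16-week change adjusted for baseline. The article instead supplies a difference in walk distance between patients with and without mildly elevated pressure. No sentence explains why sildenafil should recover 45 of the roughly 50 m, and no correlation or residual SD connects the 75 m to adjusted change. The PAC figure has the same origin.

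The abstract says the results will inform a phase 3 study. A non-significant result read against a claim of more than 80% power would look like reasonable evidence against a 45 m effect. If true power is far lower, that reading would mislead the planning of the next trial.

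**Working it through.** **Inputs.** Effect 45 m, source gap about 50 m, SD 75 m, 27 completers, 30 enrolled, drop-out 10% or 17% (Sample size); two-sided 0.05 (Data analysis plan); 1:1 allocation (Interventions); 39 m (Background); 33 m and 24 m (Outcomes). Completers are split 14 and 13.

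**Share of the gap.** 45/50 = 90%, approximate because the 50 m is approximate. On the same scale, 39 m is 78%, 33 m is 66% and 24 m is 48%.

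**Drop-out.** 27/0.9 = 30, as stated. At 17%, 30 × 0.83 = 24.9, or about 25 completers.

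**The plan's own power.** Two arms, SD 75 m: SE = 75 × √(1/14 + 1/13) = 28.9 m. The noncentrality is 45/28.9 = 1.56 on 25 df, and power is 32%. A normal approximation gives 34%. Neither reproduces more than 80%. A one-sample (or paired) t-test gives 85% with n = 27 and 82% with n = 25, which fits both stated claims.

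**Two-arm power with SD 75 m** (noncentral t, 25 df):

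| Difference | Power |
|---|---|
| 45 m | 32% |
| 39 m | 25% |
| 33 m | 20% |
| 24 m | 13% |

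**Allowing for baseline adjustment.** If 75 m is the SD of walk distance and r is the correlation between baseline and week 16, the residual SD is 75 × √(1 − r²). The article gives no r, so the values below are assumptions. Three df are removed for baseline, age and sex (22 df).

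| Assumed r | Residual SD | Power at 45 m | Power at 39 m |
|---|---|---|---|
| 0.5 | 65.0 m | 41% | 32% |
| 0.7 | 53.6 m | 55% | 44% |
| 0.8 | 45.0 m | 70% | 58% |

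Power of 80% at 45 m needs a residual SD of about 40 m. Since 75 × √(1 − 0.85²) = 39.5 m, that means r of about 0.85.

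**PAC at its own stated values.** With 0.6 mL/mmHg and SD 1.1, two-arm power is about 28%, against the stated 80%.

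**What a null result could exclude.** The 95% confidence interval half-width is 2.06 × 28.9 = 59 m with SD 75 m. With r = 0.8 it is 2.07 × 45 × √(1/14 + 1/13) = 2.07 × 17.3 = 36 m. In both cases an estimate of zero would leave the 33 m and 24 m MIDs inside the interval.

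**The case against.** Several replies have force.

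- **45 m is not out of line.** The 39 m in the Background is of the same order, and Interventions cites a PAH trial in which sildenafil did better than an ERA on 6MWD. On the article's own reasoning, a target 6 m above an ERA's result can be defended. This stands. Nor is 39 m the correct target: it comes from a different drug class, and the article itself counts the mixed cohort as a limitation.
- **The disease gap need not be a ceiling.** A reader might infer that the trial is sized only for near-complete reversal of the deficit, and so for an unattainable effect. Nothing in the article says that the gap limits what treatment can add, so that inference is not supported.
- **The text partly uses the right label already.** Later in the Sample size section, and in the Figure 3 caption, the language is of detectable alternatives. The opening still calls 45 m an effect size estimate, so the wording is inconsistent. Figure 3 is not shown and may give power at other differences.
- **The SD point works in the plan's favour.** Adjustment for baseline would raise power. This is true, and it is why the range over r is shown.
- **Misreading is partly guarded against.** The article admits that 45 m exceeds the PAH MID, plans responder comparisons at 24 and 33 m, and regards a result of no difference as useful. None of this corrects the stated power.

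The RV strain difference is also taken from elsewhere ("this is the difference detected in our ATPAHSS Study of ambrisentan and tadalafil in treatment naïve SSc-PAH patients after therapy"). What it represents depends on cited studies not at hand, so it is not counted here. Any figure for partial recovery of the PAC gap would likewise be invented.

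**Conclusion.** The point holds in a limited form. The effect and, apparently, the SD come from a cross-sectional, non-treatment contrast, and so does the PAC difference. The stated power above 80% is not delivered for the planned two-arm test: it is about 32% at 45 m with SD 75 m, and about 41% to 70% if r is assumed to lie between 0.5 and 0.8.

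Most of the shortfall comes from the two-arm arithmetic. Replacing 45 m by 39 m lowers power only from 32% to 25%, while using a residual SD raises it. The choice of 45 m is therefore optimistic, and it is not the main cause of the low power. That a one-sample formula was used is an inference from the match with the stated figures; the article does not say so. That 75 m is an SD of walk distance is the natural reading of the sentence, but it cannot be confirmed because the preliminary data are not shown.

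**What to change.** In the Sample size section, with enrolment kept at 30:

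1. Describe 45 m and 0.6 mL/mmHg consistently as detectable alternatives, and say that they come from a comparison of SSc-MEP with normal-pressure SSc, not from a treatment contrast.
2. Replace the 75 m SD with the residual SD of 6MWD change given baseline. If no repeat-walk data are available, show power over a stated range of correlations.
3. Replace the claim of more than 80% power with two-arm power at 45, 39, 33 and 24 m.
4. State that a non-significant result will be interpreted from the confidence interval for the treatment difference against the cited MIDs of 24 and 33 m.

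The cost is recalculation and a few sentences of text. No patients, visits or procedures are added. The downside is a less favourable stated power.

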Sildenafil is being purchased from Teva Pharmaceuticals, who are not involved in the planning or conduct of this trial. Participants are randomized to either sildenafil (20 mg) or matching placebo taken three times per day. Sildenafil and placebo tablets are being over-encapsulated by the Research Pharmacy at the Johns Hopkins University (JHU) School of Medicine Research Pharmacy. At the Research Pharmacy, capsules are being packaged into bottles with a liner, cotton, and childproof cap. One bottle of drug product is dispensed to study subjects at the baseline study visit and at the 16-week visit during the treatment phase. Subjects are asked to return bottles at the 16-week and 52-week visits to allow for tracking of adherence and medication control. Randomization to drug or placebo is done in a 1:1 fashion blocked and stratified by center. All study personnel, subjects, and the statistician are blinded for the duration of the study until the last subject completes follow-up assessments. The JHU Research Pharmacist is unblinded. In the rare event that unmasking is necessary for clinical care, the Chair of the Steering Committee will make the decision to unmask, and the treating physician will call the research pharmacy to obtain the participant’s treatment assignment. Subjects will be withdrawn from the trial if the participant withdraws consent or if the principal investigator determines that the subject should be withdrawn for safety. One specific scenario in which this could occur is if the participant has a mPAP > 25mmHg and a PAWP ≤ 15mmHg on their week 16 RHC; they would be withdrawn from the trial and given guideline-based PAH treatment.

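### The stated power above 80% for a 45 m difference with 27 subjects does not follow from the plan's own inputs; a two-arm comparison gives about 32%

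*Protocol article*

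**What the plan says.** All points are from the protocol article.

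- **Sample size.** The target effect on six-minute walk distance (6MWD) is 45 m. It comes from unpublished preliminary data in which SSc patients with normal pressure and patients with mildly elevated pressure differed by roughly 50 m, "with a standard deviation of 75 m". From this the section concludes that "we will have > 80% power to detect this difference at significance level of 0.05 with 27 subjects".
- **Drop-out, same section.** "To account for a 10% drop-out rate, we are enrolling 30 subjects". If drop-out rises to 17%, "we maintain adequate power to detect a difference of 45 m with 80% power".
- **Interventions.** "Randomization to drug or placebo is done in a 1:1 fashion blocked and stratified by center".
- **Data analysis plan.** "Hypothesis testing will use two-sided α = 0.05 without correction for multiplicity". For the primary outcome, "The primary analysis will compare the absolute change in 6MWD from baseline with adjustment for baseline 6MWD, age, and sex in linear regression models".

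No SD of change, residual SD or baseline to week-16 correlation is given. Fig. 3, which is captioned as showing power and detectable alternatives by sample size, was not available for this check.

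**The concern.** A difference of 45 m with an SD of 75 m is a standardized effect of 0.60. Thirteen or fourteen patients per arm cannot give 80% power for an effect of that size in a two-arm comparison, so the claim looked wrong by a wide margin.

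The SD is also of a doubtful kind. It describes how patients differ from one another in a cross-sectional comparison. It is not shown to be the SD of change or the residual SD of the adjusted model, and one of these determines the power of the planned analysis.

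At stake is how the result is read. The Abstract says the results will inform a phase 3 study. If the trial is described as more than 80% powered for 45 m, a null result will tend to count as evidence against a 45 m effect. If the power is nearer one third, a null result says little about it.

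**Working it through.** **Inputs.** Difference 45 m, SD 75 m, 27 completers, 10% drop-out (Sample size); 1:1 allocation (Interventions); two-sided 0.05 (Data analysis plan). Since 27 / 0.90 = 30, the 27 is the total for both arms: 13 and 14.

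**Formula.** SE = SD × √(1/n₁ + 1/n₂). Noncentrality = difference / SE. Power is the probability that a noncentral t variable with n₁ + n₂ − 2 degrees of freedom falls beyond the two-sided 5% limits.

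**Step 1: the plan's figure as a two-arm comparison.**

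SE = 75 × √(1/13 + 1/14) = 28.9 m; noncentrality = 45 / 28.9 = 1.56; critical t (25 df) = 2.06; power = **32.2%**.

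| Reading, difference 45 m, SD 75 m | Power |
|---|---|
| 13 vs 14, two-sided | 32.2% |
| 13 vs 14, normal approximation | 34.4% |
| 12 vs 13 (17% drop-out: 30 × 0.83 = 24.9) | 30.1% |
| 15 vs 15 (no drop-out) | 35.5% |
| 13 vs 14, one-sided | 44.9% |
| 27 per arm (contradicts enrolling 30) | 58.1% |

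Using the observed 50 m instead of 45 m gives 38.4% for 13 vs 14. None of these readings reaches 80%.

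With 13 vs 14, the difference detectable at 80% power is 84 m. An unadjusted test is significant only if the observed difference exceeds 2.06 × 28.9 = 59.5 m. Power of 80% for 45 m needs 45 per arm, 90 completers. For the 39 m difference that the Background reports from the earlier ambrisentan trial, power is about 25%.

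**Step 2: what does reproduce the claim.** For a one-sample or paired test, SE = 75 / √27 = 14.4 m and noncentrality = 45 / 14.4 = 3.12.

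| One-sample t, two-sided | Power |
|---|---|
| n = 27 | 85.1% |
| n = 25 | 82.1% |
| n = 24 | 80.4% |

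This fits both the claim above 80% and the claim of 80% at 17% drop-out. The global RV strain statement points the same way. Its effect of 4.8 with SD 8 is also 0.60, and the section claims more than 85%. One-sample gives 85.1%; two-arm gives 32.2%.

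**Step 3: can the adjusted primary analysis rescue the claim?** Take 75 m as the cross-sectional SD at each visit and let r be the correlation between baseline and week 16 (an assumption; the article gives none). The residual SD is then 75 × √(1 − r²). With three covariates and 27 completers there are 22 df.

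| r (assumed) | Residual SD | Power for 45 m | Detectable at 80% | Smallest significant difference |
|---|---|---|---|---|
| 0.5 | 65.0 m | 41% | 73 m | 52 m |
| 0.7 | 53.6 m | 55% | 60 m | 43 m |
| 0.8 | 45.0 m | 70% | 51 m | 36 m |
| 0.85 | 39.5 m | 81% | 45 m | 32 m |

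Power of 80% needs r of about 0.85 with 27 completers and about 0.86 with 25. For 39 m, power at r = 0.7 is 44%.

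If 75 m is instead the SD of change, and the SD is equal at both visits, the residual SD after baseline adjustment is 75 × √((1 + r)/2). For any r of zero or more this is at least 75 / √2 = 53 m. That is close to the r = 0.7 row, so power stays near 55% at best.

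**The case against.** The strongest counter-argument is that 32% belongs to a test that is not the primary analysis. The plan adjusts for baseline 6MWD, so the relevant SD is a residual SD, and at r = 0.85 the claim comes out right. This stands in part. The claim is not impossible, and two consequences depend on r. On the adjusted analysis, the chance of missing a true 45 m effect is about 59% at r = 0.5, 45% at 0.7 and 30% at 0.8. From r = 0.7 upward, a significant result no longer needs an observed difference above 45 m. But the section derives its power directly from 45 m and 75 m, does not attribute it to adjustment and states no correlation.

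Second, the one-sample explanation is an inference. It fits 6MWD and RV strain, but not every secondary claim of 80% or more: one-sample t gives 63% for TAPSE, 78% for PAC and 79% for RVEF. Fig. 3 might show the method. So the cause is probable, not proven. The finding does not depend on it.

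Third, the Data monitoring section calls this a phase II trial that is useful even without a difference, and the plan adds comparisons of the proportions reaching a minimal important difference. That softens the harm. It does not make the printed power correct.

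**Conclusion.** The concern holds. On the stated inputs (45 m, SD 75 m, 27 completers in two equal arms, two-sided 0.05), power is 32% against a stated figure above 80%. At 17% drop-out it is 30% against a stated 80%. On those inputs the trial would miss a true 45 m effect about two times in three. A significant unadjusted result would need an observed difference of about 59 m, which exceeds the design effect and would tend to exaggerate the benefit.

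For the planned adjusted analysis, power lies between 41% and 81% for assumed correlations of 0.5 to 0.85, with 75 m read as the cross-sectional SD. The printed claim is met only at the top of that range. The most likely origin is a one-sample calculation applied to a two-arm trial. An unseen analysis plan could supply the missing correlation, but it would not make the printed derivation valid.

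**What to change.** Keep the enrolment of 30 and correct the Sample size section:

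1. State that 27 completers in two arms give about 32% power for 45 m with an unadjusted two-sided test at SD 75 m, and a detectable difference of about 84 m.
2. Take the SD of change, or the correlation between repeated 6MWD measurements, from the sponsor's preliminary data. Give power and detectable difference for the planned regression at that value and over correlations of 0.5 to 0.85, and say which kind of SD the 75 m is.
3. Delete the claim of 80% power at 17% drop-out. It could return only if those data support a correlation of about 0.86 or more.
4. Check Fig. 3 and redraw it for a two-arm comparison.
5. State that the result will be interpreted through the treatment difference and its 95% confidence interval, and that a non-significant result will not be read as absence of a 45 m effect.

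The cost is a rewritten paragraph and one figure. No patients, visits or analyses are added. The stated power becomes less favourable.

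### The secondary-endpoint power claims (80% or greater with 27 completers) are wrong for a between-arm comparison: the stated inputs give 21% to 43%, and TAPSE falls short even under a one-sample formula

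*Protocol article*

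**What the plan says.** The Sample size section makes a blanket claim: with 27 completers, "we also have adequate power (80% or greater) to detect differences in the proposed secondary outcome measures". It then goes through the endpoints.

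- PAC: "we have 80% power to detect a mean difference in PAC of 0.6 mL/mmHg (SD 1.1) between treatment arms".
- TAPSE: "we will have sufficient power to detect differences of 0.23 cm (SD 0.5) in TAPSE between groups".
- Global RV strain: "we have more than 85% power to detect a difference of 4.8% (SD 8" percent).
- RVEF: adequate power for 5% (SD 9%), described as a contrast between arms.
- SF-36 and emPHasis-10: adequate power for 5 units (SD 7) and 6 units (SD 10).

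Only PAC and RV strain carry a percentage of their own. The other four are called adequate or sufficient, so their figure is the blanket 80% or greater. NT-proBNP has no difference or SD and cannot be checked.

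**The concern.** The contrasts are described as between arms, and 27 is the total number of completers. With about 13 or 14 patients per arm, standardized differences of 0.46 to 0.71 cannot be detected with 80% power by an unadjusted comparison. The claims are also inconsistent among themselves. TAPSE has a smaller standardized difference (0.23/0.5 = 0.46) than PAC (0.6/1.1 = 0.545) at the same sample size and significance level. If PAC has 80% power, TAPSE must have less, yet it is covered by the same claim of at least 80%.

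RV function and health-related quality of life are the second and third stated aims, and PAC is put forward as a measure that may be modifiable early in disease. The Sample size section ties the TAPSE and RVEF differences to minimal important differences and calls the quality-of-life differences clinically relevant. A reader who believes the power claims could take a null result as evidence against effects of that size. The Abstract says the results will inform a phase 3 study, so the precision of these endpoints needs to be stated correctly.

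**Working it through.** **Inputs**

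- Completers: 27 in total ("Based upon a sample size of 27 subjects completing the trial, we also have adequate power (80% or greater"), from 30 enrolled ("To account for a 10% drop-out rate, we are enrolling 30 subjects"; 30 × 0.9 = 27).
- Allocation: "Randomization to drug or placebo is done in a 1:1 fashion blocked and stratified by center" (Interventions), so 14 and 13.
- Test: "Hypothesis testing will use two-sided α = 0.05 without correction for multiplicity", with independent t-tests (Data analysis plan).
- Differences and SDs: Sample size section, as listed above.

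**Formulas**

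- Two-sample: noncentrality λ = d / √(1/14 + 1/13) = d / 0.3852, with d = difference/SD, 25 degrees of freedom and critical t = 2.060.
- One-sample: λ = d × √27 = 5.196 d, with 26 degrees of freedom and critical t = 2.056.
- Power is the noncentral-t probability beyond the critical values.

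**Trying to reproduce the stated figures.** The one-sample formula on all 27 comes closest. For RV strain, λ = 0.60 × 5.196 = 3.118 and power is 85.1%, against a stated figure of more than 85%. For PAC, λ = 0.5455 × 5.196 = 2.834 and power is 77.9%, or 80.9% by the normal approximation, against a stated 80%.

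**The comparison the article describes.** For PAC, λ = 0.5455 / 0.3852 = 1.416 and power is 27.5%. For RV strain, λ = 0.60 / 0.3852 = 1.558 and power is 32.2%.

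| Endpoint | Difference / SD | d | Stated power | Two arms, 14 vs 13 | One sample, n = 27 |
|---|---|---|---|---|---|
| PAC (mL/mmHg) | 0.6 / 1.1 | 0.545 | 80% | 27.5% | 77.9% |
| TAPSE (cm) | 0.23 / 0.5 | 0.460 | sufficient | 21.0% | 63.4% |
| RV strain (%) | 4.8 / 8 | 0.600 | more than 85% | 32.2% | 85.1% |
| RVEF (%) | 5 / 9 | 0.556 | adequate | 28.4% | 79.4% |
| SF-36 (units) | 5 / 7 | 0.714 | adequate | 43.0% | 94.6% |
| emPHasis-10 (units) | 6 / 10 | 0.600 | adequate | 32.2% | 85.1% |

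**Detectable differences at 80% power.** With 14 vs 13, the standardized difference needed is 1.123, so each detectable difference is 1.123 × SD.

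| Endpoint | Stated | Detectable at 80% | Ratio |
|---|---|---|---|
| PAC | 0.6 | 1.24 | 2.1 |
| TAPSE | 0.23 | 0.56 | 2.4 |
| RV strain | 4.8 | 9.0 | 1.9 |
| RVEF | 5 | 10.1 | 2.0 |
| SF-36 | 5 | 7.9 | 1.6 |
| emPHasis-10 | 6 | 11.2 | 1.9 |

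**More generous readings**

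- One-sided 5% test: 31.5% to 56.3%.
- All 30 patients analysed, 15 per arm: 22.9% to 47.2%.
- 27 per arm, which contradicts the enrolment of 30: 38.2% to 73.1%.
- Baseline adjustment, if the stated SDs are for raw values: the SD shrinks by √(1 − r²). At an assumed r = 0.5 power is 26% to 54%; at r = 0.7 it is 36% (TAPSE) to 70% (SF-36); at r = 0.8 it is 48% (TAPSE) to 84% (SF-36).
- Correlation needed for 80%: r = √(1 − (d/1.123)²). For SF-36, √(1 − 0.636²) = 0.77; for PAC, √(1 − 0.486²) = 0.87; for TAPSE, √(1 − 0.410²) = 0.91.

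**The case against.** The strongest objection is that the planned secondary analysis is a regression adjusted for baseline and sex, not an unadjusted t-test, and that the article does not say whether each SD is for a raw value, a change score or a residual. If the SDs are raw, the unadjusted 21% to 43% understates the power of the planned model, and at a correlation of 0.8 SF-36 would meet its claim. This stands as a qualification: true power depends on an input the article does not give. It does not support the stated figures. No correlation is stated, the other five endpoints stay below 80% even at r = 0.8, and if the SDs are already for change scores or residuals most or all of the credit disappears.

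Three narrower points also stand.

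- The one-sample origin is an inference from two percentages, and the power figure (Fig. 3) is not available to confirm it. The error does not depend on it.
- Only TAPSE and RVEF are tied to a minimal important difference. The PAC value is a difference between patient groups in preliminary data, and the strain value was observed in an earlier treatment study.
- The article does not say that null secondary results will be presented as evidence of no effect; that is a risk of misreading.

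Finally, a 30-patient phase 2 trial need not be powered for secondary endpoints, and no analysis changes as a result. That is true, but the article asserts the power with numbers, and the numbers are wrong.

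**Conclusion.** The concern holds. On the stated differences and SDs, with 27 completers split 14 and 13 and a two-sided 5% t-test, power is 21% to 43%, against a claim of 80% or greater (more than 85% for RV strain). No between-arm reading with 27 or 30 patients in total reaches 80% without an unstated baseline correlation of at least about 0.77. The TAPSE claim fails under the one-sample formula as well. The size of the shortfall assumes that the stated SDs apply to the quantity being compared; if they are raw SDs, baseline adjustment narrows the gap but closes it for none of the six at r = 0.7 and only for SF-36 at r = 0.8.

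**What to change.** In the Sample size section, delete the blanket 80%-or-greater claim and the endpoint-specific statements of 80%, more than 85%, adequate and sufficient power. Replace them with a short table giving, for each secondary endpoint, the two-arm detectable difference at 80% power (1.123 × SD) or the expected 95% confidence-interval half-width (2.060 × 0.3852 × SD = 0.793 × SD; for PAC, 0.87 mL/mmHg) with 27 completers. State what each SD refers to, and show a second column under a stated baseline correlation if credit for adjustment is wanted.

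Describing the secondary results as estimates with confidence intervals would suit this precision, but it is optional and does not follow from the arithmetic.

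The cost is one rewritten paragraph, with no extra patients and no change to the analysis. The stated figures become less favourable.
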